### Trial status

The first participant recruitment began on 11 May 2020.

### Participant safety and withdrawal

The researcher’s name and phone number for an emergency contact will be provided to ensure the patient’s safety. All participants are informed that they can voluntarily discontinue the study at any time and they could be withdrawn when the significant disease non-related to study is detected, cancer metastasis and recurrence occurs, or if they did not follow the instruction of doctor in charge.

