### Interventions

#### Personalized digital therapeutic (intervention) group

For the personalized digital therapeutic group, Colon Cancer by Second Doctor program (Medi Plus Solution, Seoul, Korea) for health management after colorectal cancer surgery and DoFit as a smart band on the wrist (NF-B20, Medi Plus Solution, Seoul, South Korea) will be used. The application and fundamental contents are developed by an expert team consisting of app developers, designers, service programmers, cancer rehabilitation specialists, and researchers as the basis of evidence. It can be used on both Android and iOS platforms. Data collected from smart band can be transferred to application via Bluetooth connection. This smart band is capable of measuring the physical activity (step counts and energy expenditure), heart rate through a built-in 6-axis accelerometer, gyroscope, and photoplethysmography sensor. In addition, information from smart devices such as blood pressure monitors, blood glucose monitors, and weight scales can be linked with the application.

The key app functions are indicated in Table 1 and screenshots of representative functions are shown in Fig. 2. User information for the algorithms of personalized content includes treatment type (chemotherapy), hypertension, initial weight, age, perceived rating of exertion, and comorbid diseases. After the primary analysis using these factors, the user life log data is repeatedly analyzed to provide a tailored guide.

Health care professionals can monitor the individual usage of participant using a web-based open architecture management program including all life log data. To manage the adherence to the mHealth-based intervention, we will monitor the application usage rate every 2 weeks for 12 months, and feedback will be provided during initial 3 months.

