### Primary outcome

The primary objective of this study is to determine the effect of mobile application and wearable smart band in the management of prognostic factors in colorectal cancer patients. Therefore, the primary outcome would be the skeletal muscle mass increment in the intervention group compared to the control group in 12 months from the baseline, measured using the bio impedance analysis.

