### Sample size calculation

Based on a previous study [24], the sample size was calculated with effect size of 0.35 (moderate level), 80% of power, and allocation ratio 1 (control group): 2 (intervention group) using the G-power 3.1.9.2. The results showed that the number of intervention and control group participants were at least 195 and 97, respectively. Considering the drop-out rate (10%), total number of participants was 324 (216 of intervention group and 108 of control group). We will enroll competitively participants to reach target sample size.

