### Statistical analysis

All data will be analyzed using IBM SPSS Statistics version 28.0.1 (Armonk, New York, USA) and a significance level of 5% will be set with a 95% confidence interval. Patient demographics will be calculated using descriptive statistics. Kolmogorov–Smirnov test will be performed to assess the distribution of data. To compare baselines between the two groups, a student’s t-test and chi-squared test will be conducted. In case the randomization is not balanced, the baseline difference will be corrected through multivariate logistic regression and analyzed. To compare the mean difference, if the primary outcome (skeletal muscle mass) data in both groups are found to be normally distributed, we will perform an independent t-test. Missing data will be handled depending on the distribution of data after study completion. To investigate the effects of the interventions and differences between groups for secondary outcomes, a mixed effects model or generalized estimating equations will be conducted, with one between-subject factor (group) and one within-subject factor (evaluation time).

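### Withdrawal from the study for recurrence, new disease or non-compliance is not separated from the end of follow-up, so the 12-month primary outcome can be lost selectively and the randomised comparison biased in a direction not known in advance.

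*Protocol article*

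**What the plan says.** Under Participant safety and withdrawal, participants are told that "they can voluntarily discontinue the study at any time and they could be withdrawn when the significant disease non-related to study is detected". The same sentence adds two further grounds: "cancer metastasis and recurrence occurs, or if they did not follow the instruction of doctor in charge". The rule is permissive, applies to both arms and concerns leaving the study. It does not say whether a withdrawn participant is still measured.

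The primary outcome is "skeletal muscle mass increment in the intervention group compared to the control group in 12 months from the baseline", by bioimpedance (Primary outcome). If the data are normally distributed, "we will perform an independent t-test" (Statistical analysis). In the same section, "Missing data will be handled depending on the distribution of data after study completion".

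In the intervention group only, "we will monitor the application usage rate every 2 weeks for 12 months, and feedback will be provided during initial 3 months" (Personalized digital therapeutic group). The Control group section describes education and usual care, with no comparable monitoring. The Randomization, allocation, and blinding section describes an open study in which participant and evaluator can know the assignment.

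The sample size section allows for loss as follows: "Considering the drop-out rate (10%), total number of participants was 324".

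**The concern.** Each investigator-led ground for withdrawal arises after randomisation, and each is plausibly related to the outcome. Recurrence, metastasis and serious new disease can go with loss of muscle. So can poor compliance in a trial whose rationale is that exercise and nutrition preserve muscle. If these patients leave before their 12-month bioimpedance measurement, the patients who remain are a selected group in each arm. The selection need not be the same in both.

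Two features make unequal selection possible. The decision is discretionary and is taken in an open trial. Adherence is also more visible in the app arm, where usage is reviewed fortnightly.

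This is a matter for the protocol and not only for the analysis plan. An analysis plan can define the analysis set and the handling of missing data, but it cannot recover a measurement that was never taken.

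**Working it through.** **1. The plan's own figure.** Inputs from Sample size calculation: effect size 0.35, power 80%, allocation 1:2. The 5% level is from Statistical analysis; two-sided testing is assumed.

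- Controls: (1 + 1/2) × (1.960 + 0.842)² / 0.35² = 96.1, rounded up to 97. Intervention: 2 × 97 = 194. The plan states 97 and 195. One-sided testing would need only 76 controls, so two-sided fits.
- Noncentral-t power at 97 and 195: 80.2%.
- Drop-out: 97 / 0.9 = 107.8, so 108 controls; 2 × 108 = 216 intervention; total 324.

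The stated sample size reproduces, and the point does not depend on any error in it.

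**2. Bias formula.** Let w be the share withdrawn in an arm, and D the mean of retained minus withdrawn patients in SD units. The whole-arm mean is the retained mean minus w × D, so the retained mean overstates the arm by w × D. With the same D in both arms, a comparison of retained patients is biased by

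bias = (w_app − w_control) × D.

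The documents give neither w nor D. The values below are assumptions, with D from 0.5 to 1.

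**3. Results with no true effect.** The numbers retained are 216 × (1 − w_app) and 108 × (1 − w_control). The rejection rate is that of a two-sided 5% t-test with noncentrality bias / √(1/n₁ + 1/n₂). Positive bias favours the app.

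| Withdrawn, app vs control | Retained, app / control | Bias (SD), D = 0.5 to 1 | Share of 0.35 | Type I error |
|---|---|---|---|---|
| 10% vs 10% | 194 / 97 | 0 | 0 | 5% |
| 10% vs 5% | 194 / 103 | +0.025 to +0.05 | 7% to 14% | 5.5% to 6.9% |
| 15% vs 5% | 184 / 103 | +0.05 to +0.10 | 14% to 29% | 6.9% to 12.8% |
| 20% vs 5% | 173 / 103 | +0.075 to +0.15 | 21% to 43% | 9.2% to 22.5% |
| 5% vs 10% | 205 / 97 | −0.025 to −0.05 | 7% to 14%, against app | 5.5% to 6.9% |
| 5% vs 15% | 205 / 92 | −0.05 to −0.10 | 14% to 29%, against app | 6.8% to 12.5% |

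Example, 20% vs 5% with D = 1: bias = 0.15 × 1 = 0.15; standard error = √(1/173 + 1/103) = 0.124; noncentrality = 0.15 / 0.124 = 1.21; rejection rate 22.5%.

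Equal shares alone do not guarantee zero bias. If D differs between arms, the bias is w_app × D_app − w_control × D_control.

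**4. Power at effect size 0.35, by total loss from 324.** 10%: 80.1%. 15%: 78.0%. 20%: 75.3%. 25%: 72.6%.

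**The case against.** The strongest reply is that the text sets out a possibility and not an exclusion. Withdrawal is discretionary. Nothing says that the 12-month visit is cancelled, that data are discarded, or that only completers are analysed. A journal article condenses the full protocol, and naming the analysis set is commonly left to the analysis plan. This stands: the absence of a named analysis set is not the complaint. What remains is the rule that is stated, which takes people out of the study and does not keep them in follow-up.

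A reader might go further and infer that the rule breaks the randomised comparison in favour of the app. The documents do not support that:

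- The rule covers all participants.
- Recurrence and metastasis are not specific to one arm.
- The compliance ground refers to the doctor's instruction and not to app use.
- Usage monitoring is described as a way of managing adherence; it has no threshold and no link to withdrawal.
- Controls also receive instructions, through education, usual care and, after low anterior resection, pelvic floor training.

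A reader might likewise model removal in the app arm alone. If 10% or 20% are removed and lie 0.5 SD below their arm, the arm mean shifts by 0.10 × 0.5 / 0.90 = 0.056 SD or 0.20 × 0.5 / 0.80 = 0.125 SD. With 97 controls and the removals taken after 10% ordinary drop-out, type I error is about 7% or 16%. The arithmetic is sound, but it assumes no selective control loss and a total app-arm loss of 1 − 0.9 × 0.9 = 19% or 1 − 0.9 × 0.8 = 28%. It is an upper case, not an expectation.

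The power argument is also limited. The plan allows for 10% loss, and nothing shows that these withdrawals would exceed it.

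**Conclusion.** The concern holds as a risk to the primary comparison. Discretionary withdrawal from an open trial, for reasons plausibly related to the outcome and without stated continued measurement, can bias the 12-month result.

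The sign is unknown. A tilt towards the app is plausible because adherence is monitored in that arm only, but the documents do not say which arm would lose more. Over the assumed scenarios the bias runs from −0.10 to +0.15 SD against a planned effect of 0.35, and it is zero where withdrawal and prognosis are alike. Type I error runs from 5% to about 22.5%. A total loss of 20% instead of 10% would lower power from about 80% to 75%.

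All these figures rest on assumed withdrawal shares, an assumed gap of 0.5 to 1 SD, and an analysis restricted to retained patients. They illustrate what the rule permits and do not predict what will happen.

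**What to change.** Leave the clinical criteria as they are and amend the wording around them:

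- State that meeting a criterion may end the programme but does not by itself end follow-up.
- Keep collecting the scheduled 1-, 3-, 6- and 12-month outcomes, above all the 12-month bioimpedance measurement, unless the participant withdraws consent or dies.
- Analyse all randomised patients in their assigned arm, with any per-protocol analysis supportive only.
- Record the reason for and date of each discontinuation by arm, so that any imbalance can be seen.

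The target of 324 does not change. The cost is a wording amendment and minor effort to measure these patients at visits they would largely attend anyway, since regular outpatient follow-up is an inclusion criterion. One limit remains: recruitment has begun, so outcomes of anyone already withdrawn may not be recoverable. Their number, arm and reason should be reported.

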### Ethics and dissemination

All study procedures were approved by the Institute Review Board of three hospitals (approval numbers: SMC-2021-01-090, 2021AN0104 and KC21FNSI0177). The trial is registered on clinicaltrials.gov (approval ID: NCT05046756). The study protocol was reviewed by the institutional review board of Samsung Medical Center on 1 Feb 2021 and was approved on 23 Feb 2021 as original protocol. In the case of important protocol modifications, principal investigator will share them with coordinating investigators and trial participants, and report to the institutional review board.

Personal information about enrolled participants will be collected, shared with clinic (i.e., Korea University Anam Hospital and Seoul St. Mary’s Hospital), and retained only by the research team during study. After the end of the study, all personal information will be retained for 3 years and subsequently destroyed.

The trial results will be published in the journal and report of results will be posted on the funding institute’s site for the public, participants, and healthcare professionals.

Any publications containing the results of this study have not been already published or submitted to any journal.

## Data Availability

Not applicable.

## List of Abbreviations

CT: Computed tomography
EORCT-QLQ: European Organization for Research and Treatment of Cancer-Quality of life Questionnaire
MNA: Mini Nutritional Assessment
IPAQ-SF: International Physical Activity Questionnaire-Short Form
LARS: Low Anterior Resection Syndrome
CST: 30-second chair stand test
2MWT: 2-minute walk test
NRS: Numeric Rating Scale
eHEALS: eHealth Literacy Scale
